### Intervention

The 1-year lifestyle intervention includes intensive, family-based diet and physical activity counseling. The multidisciplinary team consists of one pediatrician, one specialist nurse, and a clinical nutritionist. Children with their parents met the pediatrician two times, the specialist nurse five times, and the clinical nutritionist three times during the 1-year intervention (Fig. 1). One of the meetings with the clinical nutritionist is only for parents and the child is with the nurse at the same time.

**Fig. 1 Fig1:**
[figure not shown]
Schedule of the intervention and the participating professionals at each intervention visit

The treatment is based on educational and behavioral counseling and motivating the participants to change their lifestyle and to support the parents in managing their children’s behavior. The aim of counseling is to increase awareness of healthy dietary and physical activity habits; to achieve a suitable energy balance, to create a positive attitude to physical activity, to promote optimal sleep duration, and to improve the children’s body image and body control.

The pediatrician performs a clinical inspection and evaluates the laboratory analyses. The participants meet the pediatrician at the baseline and at 12 months. The special nurse measures the participant’s height, weight, waist circumference and blood pressure at the beginning of the study, at 6 months and at 12 months. The nurse advises participants to modify dietary and physical activity habits and discusses sleep duration and reducing sedentary time. Dietary and behavioral counseling is delivered by the clinical nutritionist and reinforced by the whole team. Dietary guidance is based on the Nordic and Finnish nutrition recommendations [23, 24], emphasizing appropriate energy intake, regular meal frequency, quality of dietary fat, and quality of carbohydrates, including lower sugar and higher fiber intakes. This includes increasing the consumption of vegetables, berries, fruit, sources of unsaturated fats, and wholegrain products; replacing high-fat milk and meat products with fat-free and low-fat alternatives; and reducing high-fat and high-sugar snack foods and sugar-sweetened beverages. Joint family meals are encouraged.

### Physical activity

The participants in the intervention group are advised and motivated to increase their regular daily physical activity and reduce sedentary habits. They have one group session for the training in the gymnasium with a physical education instructor. The physical education instructor gives a voluntary lecture for parents about increasing physical activity and reducing sedentary time. Unfortunately, we had to cancel the group session after the start of the COVID-19 pandemic. Nevertheless, all research visits are encouraged to increase daily activity.

The entire research team encourages and motivates the participants and their parents to carry out the instructed lifestyle changes. Families are also instructed to use Finnish lifestyle internet manuals for kids and families provided by the Finnish Heart Association. Emphasis is on educational and behavioral counseling to keep up healthy growth and development with a positive attitude.

The control group continues with the normal primary care and does not receive any special intervention during the study period. Implementing intervention will not require alteration in usual care.

## Study questionnaires

All participants fill out the study questionnaires at baseline and at 12 months. Most of the study questionnaires were developed and used in the Finnish Physical Activity and Nutrition in Children Study (PANIC) [25], and thus well noticed for this age group. The study questionnaires are sent to all participants by mail and are filled out by the parents with their child at home. In the intervention group, the study questionnaires are returned during the visits at the baseline and at 12 months. In the control group, they are returned in a return envelope by mail.

### Dietary intake

Energy and nutrient intake, food consumption, and eating frequency are assessed by a food diary. The food diary includes four predefined consecutive days (three weekdays and one weekend day), and it is administered by the parents. They are instructed to record all food and drink consumption, except drinking water, of their child by household measures and to ask their child about the food and drink consumption outside the home. Food records are reviewed by a clinical nutritionist at return. Dietary intake will be calculated by the AivoDiet software, version 2.2.0.0 (Mashie FoodTech Solutions Finland Oy, Turku, Finland).

Food consumption is also assessed by the structured Food Consumption Questionnaire, developed to complete the food diary data, and used in the Finnish PANIC study [25]. Data on the quality of usually chosen foods and the frequency of consumption of selected foods are collected.

### Eating behavior

Eating behavior is measured by the Children’s Eating Behaviour Questionnaire (CEBQ) [26] administered by the parents. An official version translated from English to Finnish is used. The questions of the questionnaire represented eight categories of eating behavior: enjoyment of food, food responsiveness, emotional overeating, desire to drink, satiety responsiveness, slowness in eating, emotional under-eating, and food fussiness. Each question offers response options from never to always on a 1 to 5 Likert scale and the mean of responses of each category are calculated and used in the analyses.

### Physical activity and sedentary time

Time spent in physical activity and electronic media time are assessed by the Physical Activity Questionnaire developed for the PANIC study [27]. Physical activity includes organized sports, supervised exercise other than sports, unsupervised physical activity, physically active school transportation, physical activity during recess, and physical education. Electronic media time contains watching television and videos, using a computer, playing video games, using mobile phones, and playing mobile games.

### Sleep, socioeconomic status, and quality of life

Participants’ sleep duration and quality are assessed by the sleep questionnaire [28]. The parents are asked how many hours their child sleeps at night, how their child usually sleeps after falling asleep, how many times their child wakes up at night, how often their child snores, and how loud it is.

Participants and their parents are also asked to fill out a background questionnaire. Children’s information includes family background, experiences of being bullied for being overweight, diagnosed disorders, medications, and vitamin and mineral supplements in use. The parent’s information includes their weight and height, marital status, and lifestyle including sleep duration and quality, dietary changes, physical activity, use of alcohol, and smoking. Socioeconomic background is assessed by the annual household income and the level of education of the parents.

HRQoL is measured by a questionnaire concerning the child’s well-being during the previous 3 months including questions on the child’s psychological, physical, and social well-being [29].

### Statistical analyses

The statistical analyses will be performed using the SPSS statistical analysis software (IBM Corporation, Armonk, NY). Baseline characteristics will be compared between the intervention and the control groups using independent samples *T* test. Changes within the intervention and the control groups during the 1-year study period will be tested using paired samples *T* test and the effectiveness of the intervention will be investigated using a general linear model for repeated measures.

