#### Calculation of the sample size

Power calculation was performed based on the assumption that there would be a difference of 0.4 in the change of body mass index standard deviation score (BMI-SDS) between the intervention and the control groups. Calculations on a difference of 0.4 SD in the change of BMI-SDS, at the level of statistical significance of 0.05 based on two-sided testing and with power of 80% and the assumption that 10% of participants will drop out in both groups the estimated sample size was 40 children per group.

Thus, we aim to recruit 80 children, targeting 40 children in the intervention group and 40 children in the control group.

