## Methods

### Study visits

All participants fill out the study questionnaires and nurses measure height, weight, waist circumference, and blood pressure at baseline and at 12 months (Table 1). Participants in the intervention group have five visits to the hospital (at baseline and 3, 6, 9, and 12 months after baseline) including a total of 10 contact hours. Participants in the control group continue with the standard care in primary care. In the intervention group, all measurements of the participants are performed in the hospital. In the control group, measurements are performed in primary care. the same measurements were used in both groups. Costs in both groups will be documented. Further follow-up is possible to collect from health inspections of school health care.

**Table 1 Tab1:** SPIRIT figure of content for the schedule of enrolment, interventions, and assessments

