**Assessments:**								
*** Anthropometric measurements***			x		X^a^		x	
*** Blood pressure***			x		X^a^		x	
*** Laboratory values***			x				x	
*** Study questionnaires***			x				x	
*** Costs of the treatment***								x

^a^Only intervention group

^b^− *t*_1_ = recruitment, *t*_1_ = baseline, *t*_2_ = 3 months, *t*_3_ = 6 months, *t*_4_ = 9 months, *t*_5_ = 12 months, *t*_6_ = after the intervention period

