### Strengths and limitations

Most of the study questionnaires have been used before in other studies and thus well noticed for this age group and this study, this is one strength of our study. Second, one nurse measures the weight, height, waist circumference, and blood pressure of all subjects in the intervention group, which reduces measurement errors. On the other hand, there are five nurses, who measure subjects in the control group. This study includes some limitations that will limit the interpretability and generalizability of the findings. First, the intervention and control groups differ in measurements being taken by different providers in different locations, and thus, differential measurement bias could be the reason for any difference found between the groups. Second, parental involvement is required for children to enroll in and participate in the study, and thus, there lacks generalizability of any results to children who wish to enroll in a program like this but do not have the support of parents. Third, puberty staging is not evaluated. However, age and body height can be taken into account as a proxy for puberty staging in the analyses.

The most significant challenge of our study is the worldwide COVID-19 pandemic started in 2020. During the COVID-19 pandemic, the children studied at home and group activities such as physical activities were interrupted. Their eating habits and regular daily physical activity may have changed. Social relations also decreased significantly. These factors may affect the methods, study questionnaire may not give reliable information. The data on the quality of usually chosen foods and the frequency of consumption of selected foods and physical activities can be different than normal and can complicate the reliability of research reproducibility.

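### With only two time points common to both arms, the repeated-measures GLM is a valid test of change, but adjusting 12-month BMI-SDS for the baseline already collected would be more precise

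*Protocol article*

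**What the plan says.** The Statistical analyses section plans t-tests of baseline characteristics between groups, paired t-tests of change within each group and, for the comparison that matters, states that "the effectiveness of the intervention will be investigated using a general linear model for repeated measures", using SPSS. It names no covariate for that model.

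Under Study visits, "nurses measure height, weight, waist circumference, and blood pressure at baseline and at 12 months (Table 1" applies to all participants. Table 1 also marks anthropometry and blood pressure at 6 months, but its footnote limits these to "Only intervention group". Baseline and 12 months are therefore the only occasions on which the arms can be compared.

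The sample size section assumes that "there would be a difference of 0.4 in the change of body mass index standard deviation score (BMI-SDS") between the arms, with 80% power, 10% drop-out and 40 children per group. Its significance level is given as "at the level of statistical significance of 0.05 based on two-sided testing".

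The only mention of adjustment is in Strengths and limitations, where "age and body height can be taken into account as a proxy for puberty staging in the analyses". Baseline BMI-SDS is not mentioned there as a covariate.

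**The concern.** A repeated-measures model earns its place when both arms have several common occasions. Here there are two. Each child then contributes a single within-child contrast, the change from baseline, and the group-by-time test compares the mean of that contrast between arms. The model fixes the coefficient on baseline at 1 instead of estimating it. When the true slope of the 12-month value on baseline is below 1, part of any chance baseline difference between arms stays in the estimate as noise.

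What is at stake is precision. The target is 80 children, and the Trial status section reports that recruitment slowed and was partly interrupted, so information already collected should be used. The same reasoning applies to the blood pressure, laboratory, diet and questionnaire outcomes. If their baseline-to-12-month correlations are lower than that of BMI-SDS, the gain from adjustment is larger for them.

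**Working it through.** **Inputs from the protocol article.** Difference in change 0.4; two-sided alpha 0.05; power 80%; drop-out 10%; 40 per arm, so 40 × 0.9 = 36 evaluable per arm.

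**Inputs that the article does not give.** The SD of change, the correlation r between baseline and 12 months, and the ratio k of the 12-month SD to the baseline SD. The SD of change is back-solved below; r and k are varied.

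**1. The stated sample size.** With n = 2(1.960 + 0.842)² SD² / 0.4², an SD of change of 0.60 gives 2 × 7.85 × 0.36 / 0.16 = 35.3, so 36 per arm, and 36 / 0.9 = 40. The stated 40 is thus reproduced only with an unstated SD of change near 0.60. Solving the noncentral t for exactly 80% power at 36 per arm gives 0.597, which is used from here on. The section also says "Calculations on a difference of 0.4 SD in the change of BMI-SDS". Read as a standardised difference, that would need 99 per arm, or 110 with drop-out. That ambiguity is a separate matter.

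**2. Equivalence.** In a simulated two-arm, two-occasion data set with 40 per arm, the group-by-time F was 21.8586 and the squared change-score t was 21.8586, with the same p-value.

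**3. Variance ratio, equal SD s at both times.**
- Change score: 2s²(1 − r)
- Baseline-adjusted residual: s²(1 − r²)
- Ratio: (1 − r²) / [2(1 − r)] = (1 + r)/2

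**4. Power at 36 per arm.** The noncentrality is 0.4 / (SD × √(2/36)). For the change score it is 0.4 / (0.597 × 0.2357) = 2.84 on 70 df, giving 80%. For the adjusted model the SD is 0.597 × √((1+r)/2), on 69 df:

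| r | Variance ratio | Adjusted SD | Power | n per arm for 80% power, with 10% drop-out |
|---|---|---|---|---|
| 0.5 | 0.750 | 0.517 | 89.9% | 30 |
| 0.7 | 0.850 | 0.551 | 86.0% | 35 |
| 0.8 | 0.900 | 0.567 | 84.0% | 37 |
| 0.9 | 0.950 | 0.582 | 82.0% | 39 |
| 0.95 | 0.975 | 0.590 | 81.0% | 40 |

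Simulation with 4,000 runs per value of r gave, for change score and adjusted model in turn, 79.8% and 89.7% (r = 0.5), 80.0% and 82.8% (0.8), 80.1% and 81.4% (0.9), and 80.3% and 80.9% (0.95). The Monte Carlo standard error is about √(0.8 × 0.2 / 4000) = 0.6 points. The formula is slightly optimistic because it ignores the small cost of estimating the slope.

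**5. Unequal SDs.** The ratio becomes (1 − r²)k² / (1 + k² − 2rk). For r = 0.5, 0.7, 0.8, 0.9 and 0.95:
- k = 1.2: 0.871, 0.966, 0.997, 0.977, 0.877
- k = 0.8: 0.571, 0.628, 0.640, 0.608, 0.520

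The ratio never exceeds 1, but at k = 1.2 and r = 0.8 the gain almost disappears.

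**6. Cost in this design.** If one arm is measured with a constant offset at both visits, the offset cancels in the change score. In the adjusted model, offset × (1 − slope) remains. For an offset of 0.1 that is 0.1 × (1 − 0.9) = 0.01 at slope 0.9, 0.02 at 0.8, 0.03 at 0.7 and 0.05 at 0.5. With equal SDs the slope equals r.

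**The case against.** The planned test is valid. It addresses the same difference in change that the sample size section uses, so nothing is contradicted, and a reader who inferred an error in the plan would go too far. That stands, and the point is one of efficiency only.

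The strongest counter-argument is measurement. Table 1 places baseline after allocation. One nurse measures the intervention arm in hospital and five nurses measure the controls in primary care, and the article itself warns of differential measurement bias. Baseline is thus a covariate that may be measured differently by arm, and the change score is the more robust of the two to a constant offset. The largest precision gain (low r) also comes with the largest leak. This stands, but the leak is small: 0.05 at slope 0.5 is one eighth of the 0.4 target, and 0.01 at slope 0.9 is one fortieth. An offset that arises only at 12 months affects both analyses alike.

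It may also be said that the article allows adjustment. It allows age and height, optionally, as puberty proxies; that is not adjustment for baseline BMI-SDS.

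Four stronger readings are tempting, and the document does not support them:
- **Regression to the mean biases the comparison.** Selection on high or rising weight-for-height applies to both randomised arms, so its effect cancels in expectation. Chance imbalance adds variance, not bias.
- **Baseline adjustment rescues incomplete children.** A model of the 12-month value also loses every child without one. With 8 of 80 values missing, both methods used the same 72 children.
- **The group main effect will be taken as the result.** Nothing says so, and the sample size section defines the effect as a difference in change.
- **Leaving sex out of the puberty proxies is a fault.** The remark is an optional one among the limitations, and the full covariate list may sit in a document not shown.

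**Conclusion.** The point holds as a loss of precision in a valid analysis. With two common occasions, the planned group-by-time test is exactly a change-score t-test. Adjusting for baseline has a large-sample variance that is no greater and usually smaller.

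Under equal SDs, an SD of change near 0.6 and 36 evaluable children per arm, power rises from about 80% to 82–84% for r of 0.9–0.8, and to 86–90% for r of 0.7–0.5. The SD, r and the equality of SDs are all assumptions that the protocol does not supply. The gain is only about one point at r = 0.95 and can nearly vanish if the 12-month SD is larger than the baseline SD. The change is worth making because it needs no new data.

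**What to change.** Make the primary analysis a linear model of 12-month BMI-SDS on arm and baseline BMI-SDS, with age added if wanted, and report the adjusted difference with its 95% CI. Use the same form for the other outcomes measured at baseline and 12 months. Keep the group-by-time (change-score) result as a named sensitivity analysis; if the two estimates differ materially, discuss an arm-specific measurement offset as a possible reason.

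The cost is a change of analysis wording and one degree of freedom, with no extra visits, measurements or children. The wording should be fixed before the arms are compared. Children without a 12-month value need their own handling, which this change does not provide.

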### Ethics and dissemination

The study protocol of the HCOS study has been approved by the Research Ethics Committee of HUS. The participants receive both oral and written information about the study, and all participating children and their parents give their informed written consent. They have the right to discontinue the study without telling the reason. Research materials are stored in a locked and protected environment. Study results will be published in international scientific journals.

### Strengths and limitations

Most of the study questionnaires have been used before in other studies and thus well noticed for this age group and this study, this is one strength of our study. Second, one nurse measures the weight, height, waist circumference, and blood pressure of all subjects in the intervention group, which reduces measurement errors. On the other hand, there are five nurses, who measure subjects in the control group. This study includes some limitations that will limit the interpretability and generalizability of the findings. First, the intervention and control groups differ in measurements being taken by different providers in different locations, and thus, differential measurement bias could be the reason for any difference found between the groups. Second, parental involvement is required for children to enroll in and participate in the study, and thus, there lacks generalizability of any results to children who wish to enroll in a program like this but do not have the support of parents. Third, puberty staging is not evaluated. However, age and body height can be taken into account as a proxy for puberty staging in the analyses.

The most significant challenge of our study is the worldwide COVID-19 pandemic started in 2020. During the COVID-19 pandemic, the children studied at home and group activities such as physical activities were interrupted. Their eating habits and regular daily physical activity may have changed. Social relations also decreased significantly. These factors may affect the methods, study questionnaire may not give reliable information. The data on the quality of usually chosen foods and the frequency of consumption of selected foods and physical activities can be different than normal and can complicate the reliability of research reproducibility.

## Discussion

There are several previous lifestyle intervention studies, which have the potential to reduce BMI and decrease the risk of health problems associated with obesity [6, 15–17]. However, only seldom these are applicable in clinical work and there are only a few evaluations of the effectiveness with cost-effectiveness. This is why it will be of great importance to find out the optimal content, duration, and intensity of the treatment of overweight and obesity in children. Our study will provide new information on this.

Our study will provide new information about the effects and cost-effectiveness of lifestyle intervention in overweight or obese children in Finland. If the effects of the lifestyle intervention are positive and it is also cost-effective, the implication of our study will be of great importance to the treatment of childhood obesity, health care providers, and overweight or obese individuals.

The results of the present study will provide more information about the lifestyle and quality of life of overweight or obese children in Finland. If we can stop excessive weight gain in childhood, we might be able to help overweight children feel better and live healthier. Being overweight in childhood is associated with an increased risk of obesity and increased risk of many diseases and other discomforts such as mental and psychological issues [6]. Due to the high number of overweight or obese children, it will be challenging to take care of all the complications associated with obesity. However, the risk of health problems among overweight or obese children who become nonobese by adulthood is like those among persons who were never obese [11]. The lifetime cost is greater per child with obesity than per child with overweight and costs are greater the longer the person has been obese [12]. Because of these reasons, it is very important to try to stop excessive weight gain in childhood. If our lifestyle intervention is efficient in reducing BMI-SDS and cost-effective, the treatment model can be taken into wider use, and we can save society’s expenses.

